#### Inclusion Criteria

Participants were eligible if they met the following criteria:

Woman aged 18-55 yearsNonsmoker (confirmed by self-report and urine cotinine screening)Actively employed as laborers for ≥8 hours per day, 6 days per weekHealthy at the time of recruitmentProvided written informed consent after screening for eligibility

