**Methods:**

This prospective cohort study will recruit women working in tobacco processing who are nonsmokers and women who do not work for the tobacco industry and are nonsmokers living in a nearby area (unexposed group), with a total of 400 expected participants. The impact of TDE on health, including metabolic syndrome parameters; complete blood count; and cardiovascular, liver, renal, and lung function, will be evaluated in relation to urine cotinine levels. Air quality and chemical substances in the air and leaves will also be analyzed. The data will be subsequently analyzed using appropriate statistical tools.

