### Data Collection Method

#### Overview

Baseline data for the T-CHARM study were collected through direct, face-to-face interviews conducted by researchers, with support from physicians and trained surveyors. Data collection took place at the tobacco factory and associated workplaces. A structured questionnaire was administered, comprising closed-ended questions across multiple domains, including sociodemographic information, duration of employment, medical history, smoking status, menstrual history [11], hydration status, ergonomic concerns [12], physical activity levels [13], sleep quality [14], anxiety potential [15], and tobacco exposure assessment.

In addition to the questionnaire, a series of clinical and physiological examinations were performed to evaluate the general health status of participants. These included vital signs assessment [16], BMI calculation, ergonomic observation [17], pulmonary function testing using a portable spirometer (Contec SP10, Contec Medical System Co, Qinhuangdao, Hebei, China) [18], and venous blood sampling (3 mL) for serum analysis, including complete blood count, blood glucose, lipid profile, liver function, and renal function tests. Furthermore, a random urine sample was collected in a sterile container to analyze urine profile and cotinine levels, adjusted for creatinine concentration, using an enzyme-linked immunosorbent assay. To monitor longitudinal changes in health parameters, the same data collection protocol will be repeated every 5 years over 20 years (Figure 2).

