#### Urine Examination Procedures

Urine specimens are stored at –20 °C until analysis. Before testing, frozen samples are thawed to room temperature and thoroughly mixed to ensure homogeneity. The cotinine kit is procured from Calbiotech, El Cajon, California, and is a solid-phase competitive enzyme-linked immunosorbent assay. In this method, the sample and cotinine enzyme conjugate are added to the wells coated with anticotinine antibody. Cotinine in the samples competes with a cotinine enzyme (horseradish peroxidase) conjugate for binding sites [23]. The unbound cotinine and cotinine enzyme conjugate are removed by washing. Upon the addition of the substrate, the intensity of the color is inversely proportional to the concentration of cotinine in the sample. The cutoff level of urinary cotinine is considered to be 10 ng/mL.

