#### Bioindicator Sampling

Tobacco leaves are also collected to study the accumulation of airborne pollutants, particularly radionuclides and heavy metals, as bioindicators of environmental exposure.

Figure 3 illustrates the recruitment process for the T-CHARM study. The exposed group consisted of a total population of 2333 women who work in tobacco processing, of whom 1816 met the eligibility criteria following screening. From this eligible pool, a target sample of 200 participants was estimated and recruited. To ensure comparability, the unexposed group—women who were nonsmokers and residents of nearby communities—was also designed to include 200 participants, matched by key demographic and environmental factors. The total cohort size for follow-up is projected to reach 400 participants, with data collection encompassing baseline and longitudinal health metrics. All collected data are subjected to analysis using appropriate statistical tools, as outlined in the study’s analysis plan.

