Tobacco leaf sorters are at risk of developing neurological symptoms such as paresthesia, headaches, and dizziness, which are commonly linked to green tobacco sickness, a form of acute nicotine poisoning caused by transdermal absorption of nicotine from wet tobacco leaves [36,37]. The likelihood of absorption increases significantly when leaves are damp due to dew, rain, or sweat, particularly during early morning or humid working conditions.

Even when individuals are not employed during pregnancy, nausea experienced during pregnancy may be associated with residual effects of prior green tobacco sickness exposure, suggesting potential long-term or latent impacts. To mitigate these risks, it is essential to implement comprehensive preventive strategies aimed at minimizing direct skin contact with tobacco leaves. This includes the use of protective clothing and gloves, although such measures present practical challenges. Gloves, for instance, may interfere with the sensitivity required for leaf sorting, necessitating a careful balance between occupational safety and task performance [38].

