### Strengths and Limitations

The goal is to understand how TDE affects health over a person’s lifetime. At enrollment, the T-CHARM study collects demographic and occupational data (eg, current address, job role); lifestyle factors (eg, smoking status, dietary habits); biomarkers of exposure, including urine cotinine and other relevant indicators; and general health assessments, covering cardiovascular, respiratory, hepatic, renal, and metabolic parameters. Follow-up assessments will update exposure metrics and health status periodically, enabling dynamic tracking of disease progression and risk factors [39].

T-CHARM’s major asset is its multisource medical data integration, which includes clinical records from corporate clinics and district health centers; national health insurance data, offering continuity and completeness; and direct input from general practitioners affiliated with the research team, allowing for nuanced clinical insights beyond standard registry linkages. This approach mitigates common limitations in cohort studies, such as recall bias and loss to follow-up from self-reported questionnaires.

While traditional epidemiological studies focus on cancer, respiratory, and cardiovascular diseases, T-CHARM broadens the scope to include neurological disorders, degenerative diseases, and chronic morbidity patterns linked to environmental and occupational exposures. The longitudinal nature of general practitioner data enables detailed tracking of disease onset, progression, and comorbidities—offering a more comprehensive understanding of health trajectories in exposed populations.

Existing biases or weaknesses have been minimized, but as a cohort study, there are some limitations. The limitations include changes in characteristics of participants over time, loss to follow-up, and confounding variables that complicate data analysis due to a lack of randomization. Potential respondents are also sometimes difficult to recruit due to the invasive nature of blood collection. Additionally, biases can arise from knowledge of exposure status, participant dropout, changes in behavior due to participation, and data quality issues in retrospective studies.

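### Urine cotinine is both the nonsmoker entry screen and the exposure biomarker, so any cotinine limit within the range of occupational uptake would exclude the most exposed nonsmoking workers

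*Protocol article*

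**What the plan says.** **Entry.** The Inclusion Criteria set one nonsmoker criterion for exposed and unexposed women alike, "confirmed by self-report and urine cotinine screening". The criterion names no threshold. It does not say what happens to a woman who reports not smoking but has raised cotinine.

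**Cutoff.** Urine Examination Procedures ends its account of the assay with one figure: "The cutoff level of urinary cotinine is considered to be 10 ng/mL". This is the only cotinine cutoff in the document. Its purpose is not stated, and tobacco workers have no separate limit.

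**Exposure measure.** The Abstract says that the health outcomes "will be evaluated in relation to urine cotinine levels". Strengths and Limitations lists "biomarkers of exposure, including urine cotinine and other relevant indicators" among the data collected at enrollment. The Overview of the data collection method says that urine is taken "to analyze urine profile and cotinine levels, adjusted for creatinine concentration", so the analysis variable is creatinine-adjusted while the cutoff is not.

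**Uptake at work.** Study Implications says that leaf sorters are at risk of green tobacco sickness, described as "a form of acute nicotine poisoning caused by transdermal absorption of nicotine from wet tobacco leaves".

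**The concern.** By the document's own account, a woman who has never smoked can take up nicotine from tobacco leaves at work. Cotinine is the study's chosen marker of that uptake. A high value in a worker may therefore mean concealed smoking or heavy occupational exposure, and the document gives no rule for separating the two.

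An upper limit on cotinine at entry is then a selection on the exposure under study. In the unexposed group it mainly removes concealed smokers. In the exposed group it also removes genuine nonsmokers, precisely because they are highly exposed. Three things are at stake:

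- The retained workers resemble the unexposed women more closely than the true workforce does, so the group contrast narrows.
- The range of cotinine among workers is cut from above, so analyses against cotinine lose precision and power.
- Women excluded at baseline cannot be recovered later, and this baseline is meant to support up to 20 years of follow-up.

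**Working it through.** The document gives no cotinine distribution, no count of exclusions for cotinine, and no power or effect-size figure on this point. There is nothing to reproduce. The calculation shows only how the loss would depend on quantities that the document does not give.

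**Inputs from the document:** cutoff 10 ng/mL (Urine Examination Procedures); target of 200 exposed women (Bioindicator Sampling); significance at P<.05 (Group Comparisons), taken here as two-sided because sidedness is not stated.

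**Assumptions:** 10 ng/mL is applied as an entry ceiling. Cotinine in nonsmoking workers is lognormal, with geometric mean (GM) from 1 to 20 ng/mL and geometric standard deviation (GSD) 2 or 3. The correlation of log cotinine with an outcome is 0.30 in the full range. The 200 places are still filled after exclusions.

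**Formulas:**

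- a = (ln 10 − ln GM) / ln GSD
- share removed = 1 − Φ(a)
- λ = φ(a) / Φ(a)
- retained GM = exp(ln GM − λ ln GSD)
- k = retained SD of log cotinine / full SD = √(1 − aλ − λ²)
- correlation after truncation r′ = 0.30k / √(0.09k² + 0.91)
- power = Φ(atanh(r′) × √197 − 1.96)

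**One row in full, GM 10 and GSD 2:** a = 0, so 50% are removed. λ = 0.3989/0.5 = 0.798. Retained GM = exp(2.303 − 0.798 × 0.693) = 5.75. k = √(1 − 0.637) = 0.60. r′ = 0.181/0.971 = 0.19. Power is 0.75, against 0.99 without truncation.

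| GM (ng/mL) | GSD | Removed | Retained GM | k | r′ | Power, n=200 |
|---|---|---|---|---|---|---|
| 1 | 2 | 0.0% | 1.00 | 1.00 | 0.30 | 0.99 |
| 1 | 3 | 1.8% | 0.95 | 0.95 | 0.29 | 0.99 |
| 3 | 2 | 4.1% | 2.81 | 0.91 | 0.28 | 0.98 |
| 3 | 3 | 13.7% | 2.27 | 0.81 | 0.25 | 0.94 |
| 5 | 2 | 15.9% | 4.10 | 0.79 | 0.24 | 0.93 |
| 5 | 3 | 26.4% | 3.07 | 0.72 | 0.22 | 0.89 |
| 10 | 2 | 50.0% | 5.75 | 0.60 | 0.19 | 0.75 |
| 10 | 3 | 50.0% | 4.16 | 0.60 | 0.19 | 0.75 |
| 20 | 2 | 84.1% | 6.95 | 0.45 | 0.14 | 0.50 |
| 20 | 3 | 73.6% | 5.13 | 0.50 | 0.15 | 0.59 |

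The loss is negligible if typical worker cotinine lies far below the ceiling, and severe if it lies near or above it. The formula for r′ keeps the regression slope unchanged: the loss is in spread, correlation and power.

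**The case against.** The strongest reply is that nothing in the document ties 10 ng/mL to eligibility. The figure closes an assay description and could be an assay positivity limit. The inclusion criterion does not say that a high value alone overrides a woman's own report, and a rule for discordant results could sit in a fuller protocol. This stands as far as 10 ng/mL is concerned: a reader might infer that this limit is applied and that highly exposed workers are being removed, and the text shows neither. It does not dispose of the point. A stated entry criterion uses the exposure biomarker to confirm eligibility, and any limit low enough to fall within occupational uptake has the effect described.

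A second reply is that exposure does not rest on cotinine alone. Groups are defined by occupation, and the study also records a questionnaire exposure assessment, length of employment and particulate measurements. That is correct, and it limits the damage to analyses that do not use cotinine. Those analyses would still be made in a workforce from which the women with the highest uptake had been taken out.

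A third reply is that dropping the check in workers lets concealed smokers in. This is fair, and it rules out checking only the unexposed women: concealed smokers would then remain in the exposed group alone and could mimic harm from dust. Whatever is done must be the same in both groups.

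Three further inferences are tempting and unsupported:

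- Bioindicator Sampling reports 2333 women, "of whom 1816 met the eligibility criteria following screening". The 517 not eligible (2333 − 1816) cannot be attributed to cotinine, because the text gives no reasons; age, working hours or health could account for them.
- Because urine is frozen for later assay, a reader might infer that the 120 women already enrolled face exclusion after the fact. The Results section links the ongoing laboratory work to the second phase of baseline collection, and no exclusion for cotinine is reported.
- A reader might infer that truncation flattens the cotinine-outcome slope. Selection on the predictor alone does not bias a correctly specified linear slope.

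**Conclusion.** The point holds in conditional form. The document gives urine cotinine two roles that conflict in tobacco workers, and it offers one cutoff, of unstated purpose and on a different scale from the analysis variable. If that cutoff, or any limit within the range of occupational uptake, governs entry, nonsmoking workers are excluded for being highly exposed. The group contrast then narrows, and cotinine-outcome analyses lose range, precision and power.

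The size cannot be fixed from the document. Over the assumed distributions the share removed runs from about 0% to 84%, and the power to detect an assumed correlation of 0.30 with 200 workers runs from 0.99 down to 0.50. These figures rest on the lognormal form, the chosen GM and GSD values, and 10 ng/mL acting as the ceiling. The direction needs only an upper limit that some nonsmoking workers exceed.

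**What to change.** 1. Define nonsmoker for entry by self-report in both groups, and do not exclude tobacco workers for cotinine at or above 10 ng/mL.
2. Use cotinine as the exposure measure.
3. State what the 10 ng/mL cutoff is for, and put it on the same creatinine-adjusted scale as the analysis variable.
4. Report by group how many women lie above the cutoff, and how many, if any, have already been excluded for cotinine.
5. Prespecify a sensitivity analysis that omits women whose values suggest concealed smoking, using one high active-smoking threshold applied identically to both groups.

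The cost is a change to the eligibility wording and one extra analysis, and recruitment is still open. The downside is that a few concealed smokers may remain in the main analysis; the sensitivity analysis shows how much they matter.

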#### Exclusion Criteria

Participants were excluded for the following reasons:

Presented with fever or diarrhea, as determined by body temperature screeningHad any condition that could confound biomarker or health assessments

### Data Collection Method

#### Overview

Baseline data for the T-CHARM study were collected through direct, face-to-face interviews conducted by researchers, with support from physicians and trained surveyors. Data collection took place at the tobacco factory and associated workplaces. A structured questionnaire was administered, comprising closed-ended questions across multiple domains, including sociodemographic information, duration of employment, medical history, smoking status, menstrual history [11], hydration status, ergonomic concerns [12], physical activity levels [13], sleep quality [14], anxiety potential [15], and tobacco exposure assessment.

In addition to the questionnaire, a series of clinical and physiological examinations were performed to evaluate the general health status of participants. These included vital signs assessment [16], BMI calculation, ergonomic observation [17], pulmonary function testing using a portable spirometer (Contec SP10, Contec Medical System Co, Qinhuangdao, Hebei, China) [18], and venous blood sampling (3 mL) for serum analysis, including complete blood count, blood glucose, lipid profile, liver function, and renal function tests. Furthermore, a random urine sample was collected in a sterile container to analyze urine profile and cotinine levels, adjusted for creatinine concentration, using an enzyme-linked immunosorbent assay. To monitor longitudinal changes in health parameters, the same data collection protocol will be repeated every 5 years over 20 years (Figure 2).

**Figure 2 figure2:**
[figure not shown]
Assessment and data collection schedule.

#### Blood Examination Procedures

An automatic hematology analyzer is used to examine the complete blood count [19,20]. A small aliquot of a well-mixed blood is placed into the hematology analyzer sample holder. The analyzer uses optical and electrical methods (eg, Coulter principle) to count and characterize blood cells, including red blood cells, white blood cells, hemoglobin, hematocrit, and platelets. The reaction happens inside chambers where cells are lysed or stained as needed for measurement. The analyzer then calculates and displays complete blood count parameters such as red blood cell count, white blood cell count, hemoglobin concentration, hematocrit, platelet count, and red blood cell indices (mean corpuscular volume, mean corpuscular hemoglobin, mean corpuscular hemoglobin concentration).

An enzymatic UV test is conducted using hexokinase to examine fasting blood glucose [21]. Glucose is phosphorylated by hexokinase in the presence of adenosine triphosphate to form glucose-6-phosphate, which is then converted in the presence of NAD^+^ by glucose-6-phosphate dehydrogenase to gluconate-6-phosphate and NADH+H^+^. The increase in absorbance of NADH+H^+^ is determined spectrophotometrically at a wavelength of 340 nm as the end point measurement. Lipid parameters are assessed using standardized enzymatic methods:

High-density lipoprotein cholesterol and total cholesterol: measured via direct enzymatic homogeneous assays in accordance with International Federation of Clinical Chemistry and Laboratory Medicine guidelinesLow-density lipoprotein cholesterol: calculated using the Friedewald formula [22]Triglycerides: determined by a colorimetric enzymatic test using glycerol-3-phosphate oxidase

#### Urine Examination Procedures

Urine specimens are stored at –20 °C until analysis. Before testing, frozen samples are thawed to room temperature and thoroughly mixed to ensure homogeneity. The cotinine kit is procured from Calbiotech, El Cajon, California, and is a solid-phase competitive enzyme-linked immunosorbent assay. In this method, the sample and cotinine enzyme conjugate are added to the wells coated with anticotinine antibody. Cotinine in the samples competes with a cotinine enzyme (horseradish peroxidase) conjugate for binding sites [23]. The unbound cotinine and cotinine enzyme conjugate are removed by washing. Upon the addition of the substrate, the intensity of the color is inversely proportional to the concentration of cotinine in the sample. The cutoff level of urinary cotinine is considered to be 10 ng/mL.

#### Environment Examination Procedures

##### Air Quality Monitoring

Air quality parameters—including humidity, temperature, and other site-specific conditions—are measured inside the tobacco company to ensure compliance with standards set by the World Health Organization and the Indonesian Ministry of Health [24].

##### Inhalation Exposure Assessment

Inhalation exposure measurements involve radon, thoron, and thoron progeny. Radon (^222^Rn) and thoron (^220^Rn) concentrations are measured with a RADUET monitor (Radosys Ltd, Budapest, Hungary). The RADUET has solid-state track detectors and a thoron monitor. Radon, thoron, and thoron progeny measurements are carried out with indoor and outdoor ambient dose rate measurements. The CR-39 is chemically etched for 24 hours in 6 M NaOH solution at 60 °C to count the tracks, and the radon and thoron concentrations are calculated. The thoron progeny is measured with a stainless steel plate, CR-39, and an aluminized film. Diurnal exposure variation will also be measured with an active detector. A type ^222^Rn monitor (RAD 7, Durridge Co, Billerica, Massachusetts) measures the samples and detects alpha activity for three 24-hour periods for a short-term measurement [25].

#### Particulate Matter Sampling and Analysis

Particulate matter (PM) is collected and analyzed to determine concentration and chemical composition:

Sampling method: The 4-stage impactor is used to collect samples over 48 hours; PM fractions include total suspended particulates, PM_1_, PM_2.5_, and PM_10_.Analytical techniques: Inorganic constituents will be analyzed using Inductively Coupled Plasma Mass Spectrometry (ICP-MS/MS; Perkinelmer, Shelton, Connecticut), and cation and anion speciation is performed via ion chromatography (Thermo, Germany) [26].

#### Bioindicator Sampling

Tobacco leaves are also collected to study the accumulation of airborne pollutants, particularly radionuclides and heavy metals, as bioindicators of environmental exposure.

Figure 3 illustrates the recruitment process for the T-CHARM study. The exposed group consisted of a total population of 2333 women who work in tobacco processing, of whom 1816 met the eligibility criteria following screening. From this eligible pool, a target sample of 200 participants was estimated and recruited. To ensure comparability, the unexposed group—women who were nonsmokers and residents of nearby communities—was also designed to include 200 participants, matched by key demographic and environmental factors. The total cohort size for follow-up is projected to reach 400 participants, with data collection encompassing baseline and longitudinal health metrics. All collected data are subjected to analysis using appropriate statistical tools, as outlined in the study’s analysis plan.

**Figure 3 figure3:**
[figure not shown]
Flowchart of recruitment and participation.

### Ethical Considerations

The T-CHARM study received ethical approval from the Institutional Ethical Board in Jember, Indonesia, in July 2024 (2883/UN25.1.10.2/KE/2024) and from the Institutional Ethical Board in Kagoshima, Japan, in September 2024 (240076). Both approvals adhere to the Guideline for Ethical Clearance of Human Research and ensure compliance with national and international standards for research involving human participants. Subsequent continuation of the study was approved by the Faculty of Medicine Ethics Committee under approval number 1578/UN25.1.10.2/KE/2025.

All participants were fully informed of the study’s purpose, procedures, potential risks, and their right to withdraw at any time without consequence; screened according to predefined inclusion and exclusion criteria; and provided written informed consent before enrollment. These procedures ensure that participant autonomy, safety, and confidentiality are upheld throughout the study.

